### Secondary outcomes

To the best of our knowledge, only scale evaluations have been used to measure the outcomes of stroke rehabilitation in most previous studies. Objective outcome measurements have been used in few of them. In the present study, we will try to measure several objective parameters by using the RSscan footscan gait system (2096 mm × 469 mm × 18 mm, 16,384 sensors, 480 Hz, RSscan International, Olen, Belgium). Consisting of a sensor array, a data collector, a walkway and a computer, the footscan gait system is sensitive in detecting the parameters of plantar pressure data and time phase when subjects are standing or walking on the plate. It is designed to test the characteristics of different kinds of movement, especially among athletes[28]. Nowadays, it is also used in clinical studies to provide quantitative assessments[29, 30]. In the present study, patients will be asked to stand and walk on the plate to become familiar with the system before formal data are collected. Data of plantar force distribution, impulse, maximum force, maximum pressure and time of walk phase will be collected to evaluate lower-extremity function.

We will also assess the quality of life in both groups as secondary outcomes. The Stroke-Specific Quality of Life Scale (SS-QOL) is a patient-reported outcome measure intended to provide an assessment of health-related quality of life specific to patients with stroke[31]. The SS-QOL questionnaire consists of 49 items in the 12 domains of energy, family roles, language, mobility, mood, personality, self-care, social roles, thinking, upper-extremity function, vision and work/productivity. Scoring of the SS-QOL is rated on a 5-point Likert scale. The domains are scored separately, and a total score is also calculated, with higher scores indicating better function.

The National Institutes of Health Stroke Scale (NIHSS) is a widely used, validated tool used in nearly all large clinical stroke trials to document baseline and outcome severity of neurological impairment[32, 33]. The NIHSS comprises tests of 11 items, including the levels of consciousness, selected cranial nerves, motor function, sensory function, cerebellar function, language and inattention (that is, neglect). Total scores range from 0 to 42, with scores >25 indicating very severe neurological impairment, scores of 5 to 24 suggesting moderately severe to severe impairment and scores <5 indicating mild impairment.

### Adverse events

All unexpected adverse events during the intervention period will be reported, and the causality related to the Tai Chi intervention will be analyzed. If any adverse event occurs, the Tai Chi instructor or study managers will provide the corresponding treatment to the participant. The adverse events will be immediately reported to the primary investigator and ethics committee to decide if the participant needs to withdraw from the trial. In case of stroke recurrence or other worsening conditions, patients will be stopped from participating in the study and will be referred for further treatment.

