**Flowchart of the study design.**

### Ethics

The study protocol was approved by the research ethics committee of Dongzhimen Hospital, which is affiliated with the Beijing University of Chinese Medicine (no. 2013JS201), and it follows the principles of the CONSORT statements as well as the Declaration of Helsinki. The trial is registered with the Chinese Clinical Trial Register (ChiCTR-TRC-13003661). The research ethics committee will also be in charge of supervising all procedures carried out in our study, including patient recruitment, randomization, conduct of the study and data storage. In cases of changes to our study protocol, we have to hand in a written application to the research ethics committee. The committee members will then decide whether it is necessary to change the study protocol.

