### Randomization and allocation concealment

This study is designed as a pilot study in which 20 participants will be included in each group. Allowing for a 25% dropout rate, we will recruit 25 patients in each group which means a total of 50 patients should be included during the whole trial[19, 20]. Participants will be assigned in a 1:1 ratio according to a computer-generated randomization list. Assignments will be sealed in opaque envelopes and will be opened by the study staff following informed consent procedures and baseline testing. The participants and researchers will know the allocated group, but the outcome assessors and data analysts will not.

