### Informed consent

Prior to the study, the general study process and the responsibilities of both participants and researchers will be explained to potential participants. They will be told that their entry into the trial is entirely voluntary and that they can withdraw at any time. In the event of their withdrawal, the data collected cannot be erased and will be used in the final analyses. Written informed consent should be obtained from each participant before any interventions related to the study are started. ZL will be responsible for obtaining informed consent from all participants.

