### Statistical analysis

Statistical analysis will be conducted by statisticians who are independent from the research team using SPSS 12.0 software for Windows (IBM SPSS, Chicago, IL, USA). The categorical variables will be presented with frequencies or percentages, and the continuous variables will be presented as means and standard deviations. Demographic and clinical assessments of two groups will be compared upon admission to address the baseline characteristics. For both groups, data of primary and secondary outcome measurements collected after 4 weeks and at the end of 3 months will be compared with baseline data, respectively, to evaluate the rehabilitative effects within groups. To evaluate the effects of Tai Chi on stroke rehabilitation, data of all outcome measurements after 4 weeks and at the end of 3 months will be compared between the two groups. Unpaired two-sample *t*-tests (continuous data) and χ^2^ analysis (categorical data) will be applied in data analyses between two groups. Nonparametric methods will be used when assumptions of normality are violated. Patients with missing data before 4 weeks will be eliminated. We will also conduct an intention-to-treat analysis if participants are lost to follow-up at 3 months. The statistical significance threshold will be set at 0.05 (two-sided), with 95% confidence intervals.

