## Trial status

This trial is currently ongoing and 6 participants are still in need to complete the whole study.

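### Patients who have a recurrent stroke or worsen are taken out of the study, not only off the programme, so their later outcomes are lost because they did badly

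*Protocol article*

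**What the plan says.** The rule is in the Adverse events section of the protocol article: "In case of stroke recurrence or other worsening conditions, patients will be stopped from participating in the study and will be referred for further treatment". The sentence before it covers adverse events in general; these are "immediately reported to the primary investigator and ethics committee to decide if the participant needs to withdraw from the trial".

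Three other statements decide what happens to the data of these patients:

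- Informed consent: "In the event of their withdrawal, the data collected cannot be erased and will be used in the final analyses". This covers data already in hand and adds no later assessment.
- Statistical analysis, up to week 4: "Patients with missing data before 4 weeks will be eliminated".
- Statistical analysis, at 3 months: "We will also conduct an intention-to-treat analysis if participants are lost to follow-up at 3 months".

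On blinding, Randomization and allocation concealment states: "The participants and researchers will know the allocated group, but the outcome assessors and data analysts will not".

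**The concern.** The primary outcomes are the lower-extremity Fugl-Meyer Assessment (FMA), the Barthel Index (BI) and the Berg Balance Scale (BBS). The NIHSS and SS-QOL are secondary. A second stroke or a clinical decline is likely to worsen the scores on all of these, so the event that triggers removal is closely tied to the outcome being measured. Removing the patient from the study at that point leaves the worst outcomes unrecorded.

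Two analyses are exposed. The Statistical analysis section plans comparisons with baseline within each group, and these improve on paper when the patients who declined are absent. It also plans comparisons between groups, which are distorted if removal works differently in the two arms. That could happen because the researchers know the allocation and the article does not say what counts as worsening short of recurrence. Supervised contact differs too: controls have about 1 hour per session, while the Tai Chi arm has that plus a further 10 + 40 + 10 = 60 minutes, so a decline may be noticed more often in that arm.

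**Working it through.** **Step 1. Does the text stop the programme or the study?** The stopping sentence says study. The sentence before it speaks of leaving the trial. Neither limits the stop to Tai Chi or conventional therapy, and no section schedules an assessment after a stop. That later outcomes go unobserved is an inference, but a direct one that nothing in the article counters.

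**Step 2. What happens to the data, by time of the stop?**

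| Stopped | Data in hand | Consequence under the Statistical analysis section |
|---|---|---|
| Before week 4 | Baseline only | Removed from the analysis |
| After week 4, before 3 months | Baseline and week 4 | Can enter the 3-month intention-to-treat analysis, but only through values measured before the worsening or through imputed values |

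The method for filling missing values may stand in an analysis plan, and its absence here is not criticised. No method recovers the outcome that was not measured.

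**Step 3. Number per arm.** Randomization and allocation concealment gives 20 per group and a 25% dropout allowance: 20 × 1.25 = 25, which reproduces the stated 25. (Dividing by 0.75 would give 27.) The steps below use the stated 25.

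**Step 4. Overstatement within one arm.** Let k of 25 patients be removed, with unseen scores D points below the mean m of the rest.

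- Mean of all randomised = [(25 − k)m + k(m − D)]/25 = m − kD/25
- Mean of those observed = m
- Overstatement = kD/25

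The same formula holds for change from baseline if D is read as a shortfall in change. The scale ranges in the article set the ceiling per patient removed:

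- BI (0 to 100): 100/25 = 4.0 points
- BBS (0 to 56): 56/25 = 2.24 points
- Lower-extremity FMA (0 to 34): 34/25 = 1.36 points

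These are mathematical limits, not expected values.

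**Step 5. Shift in the between-group difference.** Shift = (k₁D₁ − k₂D₂)/25, in favour of the arm with the larger kD. With k₁ = k₂ = 2 and D₁ = D₂ = 20 it is 0. For the BI, with assumed D and an assumed net imbalance:

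| Net imbalance (patients) | D = 20 | D = 40 |
|---|---|---|
| 1 | 0.8 | 1.6 |
| 2 | 1.6 | 3.2 |
| 3 | 2.4 | 4.8 |

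**Step 6. Against the standard error.** SE = SD × √(2/25). Assumed SDs of 10, 15 and 20 give 2.83, 4.24 and 5.66.

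- SD 15: 0.8/4.24 = 0.19 and 4.8/4.24 = 1.13
- Extremes: 0.8/5.66 = 0.14 and 4.8/2.83 = 1.70

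With 20 per arm and SD 15, SE = 15 × √(2/20) = 4.74, and the range becomes 0.17 to 1.01.

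**Step 7. A milder case in SD units.** Suppose 1 of 25 patients is removed in one arm and 3 of 25 in the other (4% v 12%), with unseen scores 1 to 2 SD below the rest. The shift is (0.12 − 0.04) × 1 to 2 = 0.08 to 0.16 SD. The SE with 20 per arm is √(2/20) = 0.32 SD, so this is a quarter to a half of an SE.

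**The case against.** The strongest reply is that this is a safety paragraph in a condensed article. It tells staff to stop and refer. It says nothing about assessments or analysis sets, and a full protocol may define worsening and set visits after discontinuation. This stands in part: non-observation is inferred, and a missing definition alone would be no criticism of an article. But the sentence states a rule, and the rule as worded ends study participation.

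Second, adverse-event reporting is tied to the intervention period, so the rule may not operate after discharge. The stopping sentence carries no such limit. If it did, the patients stopped before week 4 would remain, and they are the ones who lose their place in the analysis entirely.

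Third, the exclusion from analysis comes from the Statistical analysis section and applies to missing data of any cause. That is true, but the rule here creates the missing data and links them to a bad outcome. Changing the analysis sentence alone would not bring the outcomes back.

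Fourth, the size is all assumption. The 1.70 SE extreme needs three excess removals, each 40 BI points below the rest at an SD of 10, which is 4 SD. Patients must walk at least 6 metres, and those who are unstable or worsening are excluded at entry, so many removals are not to be expected. This stands: the figures show what is possible, not what is likely.

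Fifth, the ethics committee takes part in withdrawal decisions after adverse events, recurrence leaves less room for judgement than other worsening, and the analysts are independent and blinded. These points lower the chance of differential removal. They do not restore unmeasured outcomes.

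**Conclusion.** The concern holds. By a stated rule, patients who have a recurrence or worsen leave the study, and those who do so before week 4 also leave the analysis. Missingness is therefore related to outcome. The within-group changes will look better than they were in any arm where this happens. Bias between groups is possible but not established; it is zero when removals and shortfalls are equal in both arms.

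The true size is unknown, because the article gives no recurrence or removal rate, no scores for such patients and no SD. Under the assumed inputs (net imbalance 1 to 3, D of 20 to 40 BI points, SD 15, 25 per arm) the shift is 0.19 to 1.13 SE; the milder case gives about 0.25 to 0.5 SE. This should be changed because the change is cheap. It does not invalidate a pilot trial. Confidence is medium, since later non-observation is inferred from the wording.

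**What to change.** In the Adverse events section, stop only the assigned programme on recurrence or worsening, with referral as now. Keep the patient in the study unless consent is withdrawn, with the scheduled blinded 4-week and 3-month assessments as far as the patient is able. Analyse these patients in the group to which they were randomised. Report recurrences, other worsening and removals, with reasons, by arm and out of all randomised. The clinical criteria for stopping the programme remain for the sponsor to set.

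The cost is a protocol change, for which "we have to hand in a written application to the research ethics committee", and at most a few assessments at visits already scheduled. Some balance and gait tests will be impossible for patients who are too unwell, so those data stay partly missing.

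The prospective gain is limited: "This trial is currently ongoing and 6 participants are still in need to complete the whole study". For patients already removed, the practical step is the report by arm and reason, which is still fully feasible.

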### Statistical analysis

Statistical analysis will be conducted by statisticians who are independent from the research team using SPSS 12.0 software for Windows (IBM SPSS, Chicago, IL, USA). The categorical variables will be presented with frequencies or percentages, and the continuous variables will be presented as means and standard deviations. Demographic and clinical assessments of two groups will be compared upon admission to address the baseline characteristics. For both groups, data of primary and secondary outcome measurements collected after 4 weeks and at the end of 3 months will be compared with baseline data, respectively, to evaluate the rehabilitative effects within groups. To evaluate the effects of Tai Chi on stroke rehabilitation, data of all outcome measurements after 4 weeks and at the end of 3 months will be compared between the two groups. Unpaired two-sample *t*-tests (continuous data) and χ^2^ analysis (categorical data) will be applied in data analyses between two groups. Nonparametric methods will be used when assumptions of normality are violated. Patients with missing data before 4 weeks will be eliminated. We will also conduct an intention-to-treat analysis if participants are lost to follow-up at 3 months. The statistical significance threshold will be set at 0.05 (two-sided), with 95% confidence intervals.

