## Abstract

**Background:**

As the second commonest cause of death and a major cause of disability worldwide, stroke has greatly influenced patients’ quality of life and created a huge public health burden. As a special form of physical activity that has been widely practiced in China, and even throughout the world, Tai Chi may be favorable for the rehabilitation of stroke patients. Several studies have been conducted to investigate the rehabilitative effects of Tai Chi for stroke patients, but none of them have been focused on the recovery phase (2 to 24 weeks) of stroke.

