Several studies have been conducted to explore the health-enhancing qualities of Tai Chi for stroke patients. The studies conducted by Taylor *et al*. demonstrated that community-based Tai Chi practice was a safe and feasible program for stroke patients[16, 17]. Another study indicated that a 12-posture short-form Tai Chi exercise was helpful in enhancing the standing balance of patients with a stroke history longer than 6 months after onset[18]. To the best of our knowledge, there has been no study to date in which Tai Chi was used in a rehabilitation program for stroke patients in the recovery phase (2 to 24 weeks). In this study protocol article, we will describe the rationale, design and analytic methods of a randomized controlled trial designed to investigate the rehabilitative effects of Tai Chi among hospitalized stroke patients in the recovery phase. We hypothesized that patients in the Tai Chi group would demonstrate better improvement compared with that in the control group.

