## Methods/design

### Study design and setting

The study will be conducted from 1 January 2014 to 31 December 2014 in Dongzhimen Hospital, which is affiliated with the Beijing University of Chinese Medicine. All participants will be allocated in a 1:1 ratio into either a control group or a Tai Chi group. Patients in the control group will receive standard conventional rehabilitation therapies, and a combination of Tai Chi and conventional rehabilitation therapies will be applied in the Tai Chi group. The participants’ scores on the Fugl-Meyer Assessment, Barthel Index and Berg Balance Scale will be assessed as primary outcome measures. The secondary outcome measures will be scores on the Stroke-Specific Quality of Life Scale, the National Institutes of Health Stroke Scale and the objective parameters of the RSscan footscan gait system (RSscan International, Olen, Belgium). All assessments will be conducted at baseline, 4 weeks after the rehabilitation course and at the end of 3-month follow-up. The study design is summarized in Figure 1.

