### Inclusion criteria

Participants meeting the following criteria will be included:Stroke that has been confirmed by computed tomography or magnetic resonance imagingBetween 40 and 75 years oldFirst episode of stroke or a history of stroke, but no serious deformity, and a modified Rankin Scale grade ≤2Between 2 and 20 weeks after the onset of the current strokeUnilateral lower-extremity hemiplegia and able to walk ≥6 meters [18]Blood pressure <160/100 mmHgSufficient cognition to follow commands, Mini Mental State Examination score >24No experience with Tai ChiVoluntary participation in the trial and provision of informed consent

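### Before-after comparisons within each arm are labelled as evaluating rehabilitative effects, which they cannot do; the between-group test of Tai Chi is unaffected

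*Protocol article*

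**What the plan says.** The protocol article's Statistical analysis section plans two kinds of comparison.

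- **Within each arm.** Primary and secondary outcomes at 4 weeks and at 3 months "will be compared with baseline data, respectively, to evaluate the rehabilitative effects within groups".
- **Between arms.** The next sentence begins "To evaluate the effects of Tai Chi on stroke rehabilitation, data of all outcome measurements after 4 weeks and at the end of 3 months" and goes on to compare the two groups. The method follows: "Unpaired two-sample *t*-tests (continuous data) and χ^2^ analysis (categorical data) will be applied in data analyses between two groups".

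One threshold is given for the whole section, with no exception for the within-arm comparisons: "The statistical significance threshold will be set at 0.05 (two-sided), with 95% confidence intervals".

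Two design features bear on how a within-arm change can be read. Under Inclusion criteria, patients enter between "2 and 20 weeks after the onset of the current" stroke, and the Abstract calls this period the "recovery phase (2 to 24 weeks"). Under Study design and setting, both arms are actively treated: "Patients in the control group will receive standard conventional rehabilitation therapies, and a combination of Tai Chi and conventional rehabilitation therapies will be applied". The combination goes to the Tai Chi arm, and no arm goes untreated.

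**The concern.** The stated purpose of the within-arm comparison is inferential: it is to evaluate effects. A before-after difference in a single arm has no comparator. It contains whatever recovery happens over time, practice with the tests, regression to the mean and the response to conventional therapy. In the Tai Chi arm it also contains any contribution of Tai Chi. These parts cannot be separated within one arm, so a significant change says only that scores moved.

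Interpretation is at stake. Each between-group comparison comes with two within-arm ones. For the three primary scales at two visits, that is 3 × 2 = 6 between-group comparisons and 3 × 2 × 2 = 12 within-arm comparisons. In a pilot of this size the between-group results may well be inconclusive, and within-arm p-values described as effects could then be taken as evidence. Two misreadings are possible: that both programmes are shown to work, or that Tai Chi works because its arm reached significance and the control arm did not.

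**Working it through.** The protocol gives no effect size, standard deviation or power, so it has no figure of its own to reproduce on this point. The question is how often within-arm tests would be significant if Tai Chi added nothing.

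**Inputs from the protocol**
- 20 patients per arm (Randomization and allocation concealment). The recruitment target reproduces as 20 × 1.25 = 25 per arm.
- Two-sided alpha of 0.05 (Statistical analysis).

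**Assumptions, not in the protocol**
- Tai Chi effect of zero, so both arms share the same mean gain g, in units of the between-patient SD: 0.3 or 0.5.
- Correlation r between baseline and follow-up: 0.7 or 0.8, with equal SD at both visits.
- A paired t-test. The protocol names no within-arm test.

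**Formulas**
- SD of change = √(2(1 − r)): √0.6 = 0.775 at r = 0.7, and √0.4 = 0.632 at r = 0.8.
- Standardised change δ = g / SD of change; noncentrality λ = δ√20.
- p = probability that a noncentral t on 19 df with noncentrality λ falls outside ±2.093.
- The arms are independent. Both significant = p². Tai Chi significant and control not = p(1 − p).

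| Gain g | r | δ | λ | p per arm | Both arms | Tai Chi only |
|---|---|---|---|---|---|---|
| 0.3 | 0.7 | 0.387 | 1.73 | 0.376 | 0.142 | 0.235 |
| 0.3 | 0.8 | 0.474 | 2.12 | 0.521 | 0.272 | 0.250 |
| 0.5 | 0.7 | 0.645 | 2.89 | 0.782 | 0.611 | 0.171 |
| 0.5 | 0.8 | 0.791 | 3.54 | 0.918 | 0.843 | 0.075 |

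The one-sided pattern p(1 − p) peaks at 0.25 when p = 0.5, so the figures at 0.3 SD are close to the worst case.

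**Wider range.** Expressing the common gain directly in SDs of change removes the need to assume r:

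| Gain in SDs of change | p per arm | Both arms | Tai Chi only |
|---|---|---|---|
| 0 | 0.05 | 0.003 | 0.048 |
| 0.3 | 0.25 | 0.06 | 0.19 |
| 0.5 | 0.57 | 0.32 | 0.25 |
| 0.8 | 0.92 | 0.85 | 0.07 |
| 1.0 | 0.99 | 0.98 | 0.01 |

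Significance in both arms is therefore likely only when the common gain is moderate to large. At smaller gains a chance contrast between the arms is the more likely false pattern.

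**Between-group test.** I simulated 40,000 trials per setting with r = 0.7, 20 per arm and no Tai Chi effect. The unpaired t-test rejected in 0.049 to 0.051 of trials for every common gain from 0 to 1.0 SD of change. A common gain cancels in the difference between arms.

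**The case against.** The strongest reply is that the plan already answers the question properly. The sentence after the within-arm one assigns the effect of Tai Chi to the comparison between groups. The hypothesis in the Background is also comparative, and the Tai Chi group section frames the question as what Tai Chi adds to conventional therapy. This stands. A reader might infer that the plan discards the randomised comparison, or that its test of Tai Chi is invalid. The text supports neither: the within-arm analysis stands beside the between-group one, and coming first in the paragraph does not give it priority.

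A reader might also infer that the arms will be judged by setting one within-arm p-value against the other. Nothing in the protocol says so. That is a risk of later misreading, not a planned analysis. Significance in both arms would not in itself favour Tai Chi, because the controls would show the same result.

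Two further limits stand. The protocol nowhere states or quantifies recovery without treatment; that is an inference from the name of the phase. The argument does not need it, because conventional therapy alone could move both arms. No paired test is specified either. That significance tests are meant is a reasonable inference from the general 0.05 threshold, but it remains an inference.

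What the reply does not remove is the stated purpose. The sentence claims to evaluate effects from a contrast that cannot identify them, and the section gives no caution to that end. This is wording present in the article, not a detail left to a fuller document.

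**Conclusion.** The point holds as a fault in the labelling and purpose of a supplementary analysis. Within-arm change from baseline cannot evaluate a rehabilitative effect in this design. The estimate and error rate of the between-group comparison are not affected.

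The size depends on assumed gains and correlations. If Tai Chi adds nothing, within-arm significance in both arms ranges from uncommon (14% to 27% of trials at a 0.3 SD gain) to usual (61% to 84% at 0.5 SD). The misleading one-arm pattern is at most about one trial in four. Severity is minor to moderate. I am confident that the comparison cannot serve its stated purpose, and less confident of the frequencies, which rest on values that the protocol does not supply.

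**What to change.** 1. Remove the within-group tests and the clause that gives their purpose as evaluating rehabilitative effects.
2. Report each arm's mean change at 4 weeks and 3 months with a 95% confidence interval, labelled as description only.
3. State that all conclusions on effect rest on the between-group difference, adjusted for the baseline score of the same outcome (ANCOVA in place of the unadjusted t-test).

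Items 1 and 2 are changes of wording and reduce the number of p-values. Item 3 is a small change to the planned analysis and should be recorded as such. It uses baseline scores that are already collected, so no new data are needed. The Trial status section describes the trial as ongoing, so the change can be fixed before the data are analysed.

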### Basic characteristics variables

Demographic information of the participants will be collected at baseline to describe the sample, compare conditions and investigate characteristics associated with outcomes. These measures will include participants’ sex, age, ethnicity, marital status, educational background, time since the attack of stroke, use of medication and other details. Vital signs such as respiration rate, pulse rate, resting blood pressure and body temperature will be measured by nurses.

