### Primary outcomes

The first primary outcome measurement is the recovery of motor impairment. We will apply the Fugl-Meyer Assessment (FMA) to measure it. Developed as the first quantitative evaluative instrument for measuring sensorimotor stroke recovery, the FMA is a well-designed, feasible and efficient clinical examination method that has been tested widely in the stroke population across different stroke recovery time points[21]. The FMA motor scale is recommended highly as a clinical and research tool for evaluating changes in motor impairment following stroke[22]. Its primary value is the 100-point motor domain, which has received the most extensive evaluation. It includes an assessment of the upper extremity and the lower extremity. In the present study, we will focus on the measurement of the lower extremity, which includes two subsections—the leg and coordination—with a total possible score of 34.

The improvements in activities of daily living that can be measured with the Barthel Index (BI) will be listed as another primary outcome measurement. The BI is a frequently used functional outcome measure of activities of daily living in stroke trials[23]. It is also widely used in clinical practice to assess baseline abilities, to quantify functional changes after rehabilitation and to inform discharge planning. The scale describes ten task items and is scored according to the amount of time or assistance required by the patient. These ten items are feeding, bathing, grooming, dressing, continence of bowels and bladder, transferring to and from a toilet, moving from wheelchair to bed and return, walking on a level surface for 45 meters and going up and down stairs. The total score ranges from 0 to 100, with lower scores representing greater nursing dependency[24].

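### The between-group t-test leaves out the baseline score of the same scale; it is valid under randomisation, but baseline adjustment would be a cheap gain in precision with about 20 patients per arm

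*Protocol article*

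**What the plan says.** The Statistical analysis section of the protocol article fixes the evaluation of Tai Chi: "data of all outcome measurements after 4 weeks and at the end of 3 months will be compared between the two groups". Continuous outcomes get unpaired two-sample t-tests at a two-sided 0.05 threshold, with a fallback: "Nonparametric methods will be used when assumptions of normality are violated".

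Baseline values have two uses in that section. The groups are compared at admission, and each group's later scores are compared with its own baseline. Neither is a baseline-adjusted comparison between groups; no covariate or change score is named for that comparison.

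Study design and setting and Outcome measures have every scale assessed at baseline, 4 weeks and 3 months. Under Randomization and allocation concealment, baseline testing comes before the envelope is opened, so the score is a proper pre-randomisation covariate. Basic characteristics variables also lists "time since the attack of stroke", and the Inclusion criteria admit patients between "2 and 20 weeks after the onset of the current" stroke.

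The stated hypothesis is that "patients in the Tai Chi group would demonstrate better improvement compared with that in the control group".

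**The concern.** On these scales a patient's starting score is likely to predict the later score, and entry anywhere from 2 to 20 weeks after onset suggests that patients will start from quite different levels. A t-test on follow-up scores alone treats all of that predictable variation as noise. In a trial of this size two things are at stake. The confidence interval is wider than the collected data require. And if the arms happen to differ at the start, part of that difference stays in the estimate with nothing in the analysis to remove it.

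The article names the between-group test itself, so this concerns a stated method and not a detail left to an unseen analysis plan.

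**Working it through.** **Inputs from the article.** Target of 20 per arm, 1:1 allocation, two-sided 0.05. The recruitment figure reproduces as 20 × 1.25 = 25 per arm. No effect size, SD or power is stated, so there is no power figure to reproduce. Differences below are in SD units of the follow-up score.

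**Assumption, not in the article.** r is the correlation between the follow-up score and the covariates (the multiple correlation if there are two). The range shown is 0.3 to 0.8.

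**Planned test.** The noncentrality is d × √(n/2) = d × √10 = 3.162d, on 38 degrees of freedom. At d = 0.7 it is 2.21, which gives 58% power. Power of 80% needs d = 0.91. (The normal approximation gives 0.89.)

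**Adjusted test.** With N = 40 patients and k covariates, the variance of the group difference is

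(2/n) × (1 − r²) × [1 + k/(N − k − 3)], on N − 2 − k degrees of freedom.

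The bracket is the small-sample price of estimating the covariate slopes. For k = 2 it is 1 + 2/35 = 1.057, with 36 degrees of freedom. The detectable difference is therefore about 0.909 × √(1.057 × (1 − r²)). Results with the exact noncentral t:

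| r | 1 − r² | Detectable at 80% power | Power at 0.7 SD |
|---|---|---|---|
| planned test | 1 | 0.91 SD | 58% |
| 0.3 | 0.91 | 0.89 SD | 59% |
| 0.5 | 0.75 | 0.81 SD | 68% |
| 0.6 | 0.64 | 0.75 SD | 75% |
| 0.7 | 0.51 | 0.67 SD | 84% |
| 0.8 | 0.36 | 0.56 SD | 94% |

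**Break-even.** Ignoring the small change in degrees of freedom, two covariates pay for themselves once 1.057 × (1 − r²) < 1, that is r above √(1 − 1/1.057) ≈ 0.23. With r = 0 the loss is small: 0.909 × √1.057 ≈ 0.93 SD.

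**Chance imbalance.** The standard error of the baseline mean difference is √(2/20) = 0.316 SD.
- P(gap above 0.3 SD) = 2 × [1 − Φ(0.3/0.316)] = 34%.
- P(gap above 0.5 SD) = 2 × [1 − Φ(0.5/0.316)] = 11%.

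Given a realised gap b, the unadjusted estimate shifts by r × b. At r = 0.7 that is 0.21 SD for a 0.3 SD gap and 0.35 SD for a 0.5 SD gap.

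If there is no true effect, the chance of rejection given the 0.5 SD gap is about 1 − Φ[(1.96 × 0.316 − 0.35)/(0.316 × √0.51)] = 12%. Given the 0.3 SD gap it is about 3.5%. These conditional rates lie on both sides of 5% and average to 5% over all randomisations.

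**The case against.** The strongest reply is that the planned test is not wrong, and that stands. Patients are randomised after baseline testing, so the expected baseline difference is zero. The expected difference in follow-up scores then equals the expected difference in change, and both equal the target of ANCOVA. The t-test is unbiased on average and keeps its 5% error rate.

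Some stronger readings are tempting, and the article does not support them:

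- **Wrong test for the hypothesis.** The hypothesis speaks of better improvement, and two primary outcomes are worded as change: "The first primary outcome measurement is the recovery of motor impairment" and "The improvements in activities of daily living that can be measured with the Barthel Index (BI"). A reader might infer that comparing follow-up scores fails to test the hypothesis. Under randomisation it does test it, only less precisely.
- **Bias.** The shift from an imbalance is conditional on that imbalance, is reduced by r, and averages to zero. The unadjusted standard error already includes it.
- **Time since stroke is ignored.** It is collected partly to study characteristics associated with outcome. That is a stated use, although not an adjusted group comparison.
- **The nonparametric fallback is part of the same fault.** The choice of test by distribution is a separate matter, and its detail is commonly left to an analysis plan.

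It is also fair to say that this is a pilot promising preliminary evidence, so no stated power is contradicted. That lowers the stakes. It does not remove the point, because the trial tests at 0.05 and a small sample is where precision is scarcest.

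Finally, r is unknown. These are bounded scales in patients who can already walk at least 6 metres, so r may be low for some scales and may differ between 4 weeks and 3 months. At r = 0.3 the gain is almost nothing.

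**Conclusion.** The point holds as a cheap improvement to a valid analysis. The between-group test as written does not use the baseline score of the same scale, although that score is collected for every patient.

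The imbalance probabilities, 34% above 0.3 SD and 11% above 0.5 SD, follow from 20 per arm under simple 1:1 allocation with approximately normal means. The precision gain rests entirely on the assumed r. It is negligible at 0.3, moderate at 0.5 (0.91 to 0.81 SD) and large at 0.7 or 0.8 (0.67 or 0.56 SD). The direction is secure for any r above roughly 0.23 with two covariates, and the loss below that is slight. The size cannot be stated more firmly from this document.

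**What to change.** In Statistical analysis, replace the primary between-group comparison with wording such as: at each visit, the follow-up score is analysed by ANCOVA on treatment group and the baseline score of the same scale (optionally also time since stroke onset); the adjusted mean difference with its 95% confidence interval is the result. Keep the unadjusted t-test, or its nonparametric counterpart, as a sensitivity analysis.

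ANCOVA is preferable to a t-test on change scores. The variance of a change score is 2(1 − r) times that of a raw score: equal at r = 0.5, and worse below it. ANCOVA's factor, 1 − r², is never larger than either apart from the small covariate charge shown above.

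The cost is one or two degrees of freedom and no new data or visits. It is not purely a wording change: the Ethics section requires a written application to the committee for any protocol change, and Trial status reports that only 6 participants have yet to complete. The application should be made before any group data are analysed, which is feasible because the analysts are blinded to allocation.
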